#### Household income and sources of income

Participants will be asked to report their overall household income on an incremental scale up to the median salary for Sweden, as well as their fixed outgoings (e.g. rent and bills) to enable calculation of the net income for the household. They will also be asked to select all applicable sources of income from a list, which includes all available benefits in Sweden.

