## Strengths and limitations of this study

• This study will assess the effectiveness of the Healthier Wealthier Families (HWF) model on self-reported child deprivation in Sweden by randomised controlled trial• The study design includes measures on a number of hypothesised mediators, namely self-reported financial knowledge, financial control, readiness for change, parental mental health and financial stigma, which will give insight to the intervention logic model• Data on income, and sources of income, will allow the amount of financial gain that can be attributed to the HWF model to be described• Inclusion of personal goal attainment as an outcome will allow participants to express intervention expectations in their own words and report on how far these expectations have been met• The study design includes a cost-effectives evaluation that will consider group differences in capability-adjusted life-years• An internal pilot will assess the feasibility of the RCT processes• A 12-month follow-up will allow for exploration of whether any effects are maintained in the longer-term, albeit without the ability to make group comparisons at that stage

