### Objectives

The objectives of the trial are:To evaluate whether allocation to municipal budget and debt counselling services via the HWF model and provision of a financial guidance book (intervention arm) has an effect on self-reported child deprivation in comparison to similar families who only receive the financial guidance book (waitlist-control arm).To evaluate whether allocation to the intervention arm has an effect on self-reported financial knowledge, financial control, readiness for change, attainment of personal goals to improve one’s financial situation, parental mental health and financial stigma, which relate to the model theory of change.To describe the amount of financial gain, and sources of income, that can be attributed to the HWF model.To assess whether effects on self-reported child deprivation, financial control, financial knowledge, readiness for change, personal goals, parental mental health and financial stigma are maintained 12 months post-randomisation.To estimate the cost-effectiveness of the HWF model.

It is hypothesised that, when compared with the waitlist-control arm 3 months post-randomisation, families in the intervention arm will report a lower rate of child deprivation, measured as necessary items lacking on a standardised list, due to inability to cover costs. It is further hypothesised that, when compared with the waitlist-control arm, the intervention arm will report greater financial control and knowledge, and lower levels of mental health difficulties and financial stigma.

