### Setting

The screening for the RCT will take place at children’s health care centres, known in Swedish as barnavårdscentraler (BVCs). BVCs examine the health of children (0–5 years) to monitor growth and development and provide advice and support to parents, e.g. about the child's development, breastfeeding, food and diseases. Parents are also offered vaccinations for their children at the BVC. Visits take place from just after birth until the child begins school. These services are offered free of charge and achieve excellent reach (99%) [24]. The RCT will focus on BVCs in municipalities experiencing high rates of children living in relative poverty. The 290 municipalities in Sweden have been categorised according to the proportion of children in households with income less than 60 percent of the median [20]. BVCs in the most severe categories (19.7–26.9%; and 27.0–46.0%) will be targeted for participation in the RCT. Concerning the larger municipalities, a more fine-grained categorisation will be conducted using local statistics, to be able to identify the proportion of children in households with income less than 60 percent of the median in residential areas.

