### Participants

The target population is families with children in contact with BVCs. To be eligible for the project, the parent or caregiver needs to score on one or more items that indicate economic difficulties and not have been in contact with a financial advisory service in the last month. The screening questions were developed as part of an initial adaptation and pilot study, and include items used by the Swedish Inspection of Finance. The screening includes six items covering financial worry, ability to meet costs, occupation and handling unexpected costs and current use of financial advisory service(s):During the last 12 months, have you been worried that your family will run out of money at the end of the month?During the last 12 months, have you been able to pay current expenses such as rent, bills, insurance?During the last 12 months, have you had the opportunity to buy necessary items such as clothes and food for yourself and your children?Is there at least one person in your household who currently has a paid job?Would you be able to handle an unexpected expense of 20,000 SEK (approx. £1,500) without asking for help or borrowing money?Have you used a financial advisory service within the last month? *(By that we mean if you have had a scheduled meeting with a budget and debt counselor to get help with your economy)*

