### Measures

The primary outcome measure for the RCT is child material and social deprivation (MSD). Secondary measures include household income and sources of income, financial knowledge, financial control, readiness to change, personal goal attainment, parental mental health, and financial stigma. These measures will be administered at all time points and assessed at T2 (for the RCT) and T3 (for the longitudinal cohort study). See Fig. 3 for an overview of the enrolment, intervention and assessment schedule.

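### Household income is recorded on a scale that ends at one median salary, so the mean financial gain described under objective 3 is pulled towards zero by the (unknown) share of households at the cap

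*Protocol article*

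**What the plan says.** Under Objectives, the third aim reads "To describe the amount of financial gain, and sources of income, that can be attributed to the HWF model". The list of strengths and limitations is confident that this can be done: "Data on income, and sources of income, will allow the amount of financial gain that can be attributed to the HWF model to be described".

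The instrument is described under Household income and sources of income. Participants "report their overall household income on an incremental scale up to the median salary for Sweden". The same section says that regular costs such as housing are also asked about, so that a net figure can be worked out. For sources of income, participants "select all applicable sources of income from a list"; no amount per source is mentioned. The Measures section gives the variable its role: "Secondary measures include household income and sources of income", assessed at T2 and T3.

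On who may enter, the Participants section says that "the parent or caregiver needs to score on one or more items that indicate economic difficulties" and must not have seen a financial advisory service in the last month. It states no upper limit on income. The Setting section adds area targeting: "BVCs in the most severe categories (19.7–26.9%; and 27.0–46.0%) will be targeted for participation in the RCT".

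**The concern.** The quantity asked for and the ceiling of the scale are in different units. The question covers everything the household receives; the top of the scale is a salary, which is one person's pay. A household with two earners, or one earner plus benefits, can lie above the top before the intervention starts. Its T1 and T2 answers then coincide whatever the counselling achieves.

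One route to gain is help with applying for welfare support (Intervention arm section). Such support adds to existing income, so it can occur in a household already at the top.

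At stake is whether the figure reported for objective 3 describes the gain from the model or a shrunken version of it. The response scale is fixed at data collection, so an analysis plan cannot recover amounts that were never asked for.

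**Working it through.** The article states no figure for this measure, so there is none to reproduce. The check sets the sections side by side and then illustrates the size.

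**Step 1. Is there another source for the amount?** None is described. Sources of income are a tick list. The fidelity form (Intervention fidelity section) covers attendance and topics, not money gained. Net income is reported income minus fixed outgoings: if income is stuck at the cap C at both times, the change in net income is (C − outgoings at T2) − (C − outgoings at T1), which contains no income gain at all.

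**Step 2. Can households above the cap enrol?** Yes. One positive screening item is enough, for example worry about money or being unable to meet an unexpected expense of 20,000 SEK. Area targeting does not exclude them. In the targeted categories 19.7% to 46.0% of children live below 60% of median income, so 100 − 46.0 = 54.0% to 100 − 19.7 = 80.3% do not. This shows that better-off households exist in these areas. It does not give the share above the cap, because that percentage concerns household income and the cap is a salary.

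**Step 3. What happens at the cap?** Take the median salary as 1. Two adults each on 0.6 have 2 × 0.6 = 1.2, above the top. Add a gain of 0.05: the true value goes from 1.20 to 1.25, both answers fall in the top category, and the recorded gain is 0.

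**Step 4. What happens below the cap?** Reading the incremental scale as bands, and assuming bands of 5,000 SEK, a true gain of 1,000 SEK and incomes spread evenly within bands:
- share with no recorded change: 1 − 1,000/5,000 = 0.80
- mean recorded gain: 0.20 × 5,000 = 1,000 SEK, equal to the true gain.

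Banding therefore hides small gains in individual families but leaves the group mean roughly unbiased. Only the ceiling biases the mean.

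**Step 5. How large could the bias be?** To first order, recovered fraction ≈ 1 − (share of the total gain that goes to households at the cap). If every household gains equally, this is 1 − p, with p the share above the cap: 0.90, 0.75 and 0.50 for p = 0.10, 0.25 and 0.50.

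A simulation adds the banding. All of its inputs are assumptions: lognormal household income with log-SD 0.5, the same gain for every household, band widths of 0.05, 0.10 and 0.20 of the median salary, true gains of 0.02, 0.05 and 0.10, band-midpoint coding, and one open top category coded half a band above the cap.

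| Share above cap at T1 | Households with no recorded change | True mean gain recovered |
|---|---|---|
| 10% | 10-91% | 89-93% |
| 25% | 25-92% | 73-80% |
| 50% | 50-94% | 48-57% |

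The wide middle column mostly reflects band width relative to gain. The last column is governed by the share above the cap and agrees with 1 − p.

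**The case against.** The strongest reply is that the trial recruits in areas of high child poverty and among families who report economic difficulty, with one screening item about having no paid job in the household. Few of them may be above a median salary. If the gains also go mainly to the lowest incomes, the loss is smaller than 1 − p. Both points stand: the documents do not show that many families are affected, and the example of two earners shows only that a household can exceed the cap.

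A second reply is that the article condenses a questionnaire that is not shown, so band limits and a top category may be defined there. That is fair for band width. It does not remove the ceiling, which the article states, and an open category above the median would still record zero change for those inside it.

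Some stronger readings are tempting but not supported:
- **No amount of gain can be derived.** The illustration shows attenuation that depends on an unknown share, not impossibility.
- **Coarse bands push the mean towards zero.** Step 4 shows that they do not.
- **The cost-effectiveness analysis is compromised.** Under Statistical methods it uses capability-adjusted life-years, intervention costs and societal resource use; household income is not named as an input.
- **Net income is a flawed construct.** The article defines it openly, and its Background says that ability to meet costs can improve without more income, so lower outgoings are a relevant result. How outgoings are recorded is not stated, so nothing can be said about their precision.

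**Conclusion.** The point holds as a ceiling effect. A household total is measured on a scale that stops at one earner's reference, entry has no income limit, and no other record of money gained is described. Households at the top at both T1 and T2 contribute zero gain, so the mean gain under objective 3 is biased towards zero whenever such households gain anything. The statement in the strengths list is more confident than this scale allows.

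The size cannot be fixed from the article, which gives neither the share at the cap nor the band width. Under the stated assumptions the loss is 7-11% of the true mean gain with 10% of households above the cap, 20-27% with 25%, and 43-52% with 50% (100% minus the recovered range).

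This concerns a secondary, descriptive objective. The primary outcome, child material and social deprivation, and the cost-effectiveness analysis are not affected.

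**What to change.** 1. Extend the household income scale well above one median salary, for example to at least twice it. Alternatively, ask for household income as an amount in SEK, with the extended bands as fall-back for those who cannot or will not give a figure.
2. Report household income and fixed outgoings separately as well as net income, so that a change in one is not read as a change in the other.
3. For families already enrolled on the capped scale, report the share in the top category at T1 and T2 by arm, and narrow the claim in the strengths list accordingly. Keep the existing cut-points inside the extended scale, so that a family with a capped T1 answer can be compared with its T2 answer on the same scale; otherwise the change of scale would itself look like a gain.

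The cost is a small change to the REDCap form, some more item non-response if an exact amount is asked for, and a mixture of scales among families already enrolled. If T1 collection has already closed, only the reporting steps, items 2 and 3, can still help the T1-to-T2 comparison.

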#### Financial knowledge

A selection of questions covering financial knowledge (e.g. invoice payment periods, mortgages, debt collection) and where to turn for help for better control over finances and debt management will be taken from a survey conducted by the Swedish Consumer Agency survey [9].

#### Financial control

Respondents will be asked to indicate the extent to which they agree or disagree with a series of nine statements (e.g. *My financial situation is largely outside of my control*) using a 5-point scale, ranging from 1 (strongly disagree) to 5 (strongly agree).

#### Readiness for change

To assess readiness for change, participants will be asked to complete a Readiness Ruler [14] regarding changing their financial situation. The ruler will employ a 0–10 visual analogue scale. Scores of 1–3 represent non-readiness to change, scores of 4–6 uncertainty, scores of 7–8 represent readiness, and 9–10 represent ongoing attempts at changing.

#### Personal goal

Participants will be asked to write a personal goal for improving their financial situation (*Over the next 3 months, what is your personal goal for improving your financial situation?*) at T1. Their own words will be presented back to them at T2 and T3, and they will be asked to rate how far they have achieved their goal (*On a scale of 0–10, how far have you achieved your goal: [parent’s own words inserted here]*?) A visual analogue scale ranging from anchors “not at all” for the value 0 to “extremely” for the value 10 will be used.

#### Parental mental health

The 12-Item General Health Questionnaire (GHQ-12) [7] consists of 12 items (e.g. *Able to concentrate, Loss of sleep over worry, Capable of making decisions*). Respondents are asked to rate the degree to which they have experienced a symptom during the last week with four response categories (e.g. *Less than usual, No more than usual, Rather more than usual, or Much more than usual*. The questionnaire primarily includes depression symptoms, but also some anxiety symptoms. The minimum score is 0, and the maximum is 36. A higher score indicates a higher level of distress. The Swedish version of the GHQ-12 performed excellently in a case–control study assessing discriminant validity (sensitivity = 85.5; specificity = 83.2 [11].

#### Perceived financial stigma

An 8-item measure of perceived financial stigma will be used [13]. Respondents are asked to indicate the extent to which they agree or disagree with a series of eight statements using a 5-point scale, ranging from 1 (*Definitely disagree*) to 5 (*Definitely agree*). The items cover two dimensions of perceived stigma (each consisting of four items): internalized stigma (e.g., *I feel that I am odd or abnormal because of my financial situation*) and experienced stigma (e.g., *I feel that others look down on me because of my financial situation*).

#### Demographic information and consumption of societal resources

The study will gather demographic information about the parent and their child(ren), including variables such as employment status, child age, gender. Based on previous research [1, 17], we anticipate an over-representation of participants with cognitive difficulties, non-Swedish speaking participants and single caregiver households. Due to this, demographic questions on disabilities in the household, native language and living arrangements will be included. The demographic data will be used to describe the trial sample, examine the extent to which demographic characteristics are balanced between trial arms, carry out attrition analyses, and inform the cost-effectiveness evaluation. The demographics questions will be administered at T1. Items for which the response may change (e.g. employment status, contact with health care professionals) will be administered at T2 and T3.

#### Capability index

A 6-item measure of capability [15] will be used to estimate capability adjusted life years (CALY) for the cost-effectiveness evaluation. Respondents are asked to indicate whether they totally agree, partly agree, or do not agree with a series of six statements. The items cover health, occupation, social relations, security, and political and civil rights, and financial situation (e.g. *I have an economy (salary, other income or savings) that allows me to always have a permanent home and for the most part (at least 8 times out of 10) allows me to buy what I think I need*). These questions will be administered at all time points and assessed at T2 and T3.

#### Intervention fidelity

Session attendance and the topics covered during sessions will be recorded by the budget and debt counsellors on a brief fidelity form, which will be shared with the research team to inform individual participant dose and adherence to the preventative family counselling guidance. Further to this, participant identification numbers will be checked against budget and debt counselling records. This process will identify any group contamination within the trial i.e. participants allocated to the intervention arm that do not receive counselling, or participants allocated to the waitlist control that do receive counselling.

### Data collection

T1 data collection and randomisation is planned to take place between September 2022 and June 2024. T2 data collection occurs around 3 months after T1 data collection, and is therefore due to take place between December 2022 and September 2024. T3 data collection occurs 12 months after T1 data collection and is due to take place between September 2023 and June 2025.

Data will primarily be collected using REDCap. The study questionnaire can be completed via an electronic link. Alternatively, it can be completed over the phone with a member of the research team, or on paper via post. This inclusive data collection practice allows for participant preferences to be taken into account and overcomes potential literacy difficulties that could be present in the target population. The screening form includes a question on need for interpretation, which will be consulted prior to the research team contacting the parent/caregiver to allow for necessary interpreter arrangements to be made. Participants will be offered shopping vouchers at T2 and T3 to compensate for their time completing the study questionnaire. Data will be exported into the Statistical Package for the Social Sciences (SPSS) for analysis. Participant identity numbers will be used. The file will be saved on the university server, which is automatically backed up. All data management procedures comply with current regulations on personal data management.

### Statistical methods

Baseline and demographic characteristics will be summarised using means and standard deviations (or medians and interquartile ranges) for continuous variables and percentages for categorical variables. For items that align with national survey questions, population-level comparisons will be made. Descriptive data will also be reported on process outcomes, e.g. number of families screened, proportion eligible for inclusion, and proportion consenting to participate.

The primary comparison of the trial arms will use an intention-to-treat framework. A regression analysis will be undertaken to quantify the extent to which a potential intervention effect on the primary outcome is determined by allocation to the intervention. Per-protocol comparison will be performed as a secondary analysis. Further moderation analyses will examine the associations between outcomes and participants’ characteristics. Differences in the means and proportions on measures between T2 and T3 will be assessed using parametric and non-parametric tests.

The cost-effectiveness analysis will compare the two arms of the trial at T2 follow-up using capability-adjusted life-years (CALY) gained as the outcome of interest. To analyse the cost differences between the two arms, we will collect information about intervention costs (i.e. personnel time, material, etc.) and societal resource use. We will express the final output as a cost/ CALY. Results will be presented as incremental cost-effectiveness ratios (ICER, expressing the cost per additional CALY gained). Uncertainty will be demonstrated using a cost-effectiveness acceptability curve, using bootstrapped regression estimates [5].

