## Method

### Design

A two-arm randomised waitlist-control superiority trial (1:1 allocation ratio) will be conducted to evaluate the effectiveness of the HWF model in improving the financial situation of families who have self-reported economic difficulties. The intervention arm will be referred to budget and debt counselling immediately after randomisation and the waitlist-control arm 3 months later. Informed by Patient and Public Involvement (PPI), so all participants receive some form of support at randomisation, both arms will be offered a freely available financial guidance book. RCT assessments will take place at two points: pre-intervention (T1) and post-intervention (T2; 3 months after randomisation).

A longitudinal cohort study will be conducted with all participants, from both trial arms (intervention and waitlist-control). Longitudinal assessment will take place 12 months after randomisation (T3), to assess any changes in measures between T2 and T3. See Fig. 2 for the participant timeline.

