### Sample size

The primary analysis for the RCT will be a comparison of the unweighted mean number of child material and social deprivation (MSD) items lacked (T2). The target sample size has been calculated based on this primary analysis. The power calculation has been informed by child MSD data for Sweden collected via the European Union Statistics on Income and Living Conditions (EU-SILC) survey, which reports an unweighted mean of 4.5 items lacked among the materially-deprived population. Using a significance level of 0.05 and 80% power, a total of 142 families (71 per group) will be required to detect a 1-item group difference in the unweighted mean number of child MSD items lacked, assuming a standard deviation of 3. As the trial will be conducted in areas with high rates of socioeconomic disadvantage, we estimate that up to 30% of families will experience financial hardship and be eligible for inclusion. The estimated rate of uptake is 50% among eligible families, based on a pilot in the Sandviken municipality, Sweden. Loss to follow-up is projected at 50%. See Fig. 2 for the participant timeline with projected numbers.

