## Discussion

HWF is a collaborative and sustainable model that could maximise the effectiveness of current services to address child deprivation in Sweden. The study outlined in this protocol is the first effectiveness evaluation of the HWF model in Sweden and is a crucial step before HWF can be recommended for national implementation within the child health services. However, several operational challenges are anticipated. Given that parental level of education and immigrant background have been linked to higher risk of exposure to child poverty in Sweden, the accessibility of the study questionnaire is a potential issue. The trial will operate across multiple sites and there is likely to be variation in the municipal budget and debt counselling services. As the services are freely available and open for self-referral there is also relatively high risk for trial arm contamination. However, we have put actions in place to have oversight of and try to mitigate against these risks. The study information materials and questionnaire will be made available in the languages commonly spoken in the targeted areas, and data collection can take place online, by post, or via phone. Brief counselling guidance has been developed specifically for the HWF project and will be provided to all trial sites in an effort to standardise the intervention, without compromising the personalised nature of budget and debt counselling. A fidelity checklist will be administered to record adherence to the guidance topics. Further to this, participant identification numbers will be checked against budget and debt counselling records to identify trial arm contamination.

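### The secondary per-protocol comparison is no longer a randomised one and can be biased in either direction; a complier-average causal effect should be added beside it

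*Protocol article*

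**What the plan says.** The Statistical methods section sets an intention-to-treat framework for the primary comparison and then states: "Per-protocol comparison will be performed as a secondary analysis." The article does not define the per-protocol set or name covariates for it, and it gives no other analysis of counselling received.

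The Intervention fidelity section says that counsellors record session attendance and that participant numbers are checked against counselling records. The check is meant to find "participants allocated to the intervention arm that do not receive counselling, or participants allocated to the waitlist control that do receive counselling". Receipt should therefore be known in both arms.

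The Intervention arm section lets families end counselling whenever they wish. The Discussion notes that services are open to self-referral and that "there is also relatively high risk for trial arm contamination". No rate is given for attendance after randomisation or for contamination.

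**The concern.** A per-protocol comparison, as commonly built, drops intervention families who never met a counsellor and waitlist families who found one themselves. Both exclusions follow from the family's own behaviour after allocation. What remains is attenders in one arm against non-seekers in the other, and randomisation no longer makes them comparable.

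The Background gives a reason to expect selection: it presents motivation as a condition for behaviour change and suggests that stigma keeps people away from services. If such traits also bear on how many MSD items a family lacks, the comparison mixes the effect of counselling with the kind of family that attends. Readers weighing national implementation will want the effect in families who received counselling, and the per-protocol result is the only one planned that speaks to it.

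**Working it through.** **Inputs from the article.** The Sample size section gives the scale: "to detect a 1-item group difference in the unweighted mean number of child MSD items lacked, assuming a standard deviation of 3". It also gives 71 families per group and two-sided or one-sided testing is not specified; two-sided is used here.

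**The plan's own figure.** The article states: "Using a significance level of 0.05 and 80% power, a total of 142 families (71 per group) will be required". With z-values 1.960 + 0.842 = 2.802, the two-arm formula gives 2 × 3² × 2.802² / 1² = 141.3, so 142 **per arm**. The stated 71 is what results without the factor 2 (70.6). The figure does not reproduce. That is a separate matter; here only the SD, the target difference and the group size serve as a scale. The article gives no figure for the per-protocol comparison itself.

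**Assumed inputs (none is in the article).** Attendance 60%. A motivation factor U correlates −r with MSD items at T2, r = 0.2 or 0.3. A latent tendency to attend correlates ρ with U, ρ = 0.447 or 0.707 (weight 0.5 or 1 on U plus unit noise). The true effect of counselling and of allocation is zero.

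**Per-protocol bias, no contamination.** The mean latent tendency among the top 60% is φ(−0.253)/0.6 = 0.644. The bias is −SD × r × ρ × 0.644:

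| r | ρ | Bias (items) |
|---|---|---|
| 0.2 | 0.447 | −0.17 |
| 0.3 | 0.447 | −0.26 |
| 0.2 | 0.707 | −0.27 |
| 0.3 | 0.707 | −0.41 |

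A simulation of 2,000,000 families gave the same four values; the instrumental-variable estimate was centred on zero.

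**With 10% contamination.** Removing the top 10% of controls lowers their mean tendency by φ(1.282)/0.9 = 0.195. The multiplier becomes 0.644 + 0.195 = 0.839, and the range is −0.23 to −0.53.

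**What this does to inference.** With 71 per arm and 60% attendance, about 43 attenders face 71 controls. The standard error is 3 × √(1/42.6 + 1/71) = 0.58, so biases of 0.17 to 0.41 are 0.3 to 0.7 standard errors. The two-sided false-positive rate is about 6% to 11% rather than 5%.

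**Wider range, simulated** (71 per arm, 4,000 trials per setting, no true effect). The first three rows use r = 0.3 and ρ = 0.5.

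| Uptake / contamination | Per-protocol bias | Per-protocol rejection | Complier rejection |
|---|---|---|---|
| 50% / 10% | −0.44 | 11% | 3.5% |
| 70% / 10% | −0.30 | 8.3% | 4.6% |
| 90% / 0% | −0.09 | 5.3% | 5.0% |
| All settings tried (r from 0 to 0.5) | 0 to −0.88 | about 5% to 27% | 2% to 5% |

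The complier estimate was centred near zero throughout. A larger trial does not help per-protocol: at 142 per arm its rejection rate reaches 48% in the most extreme setting.

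**Direction.** If U is unrelated to MSD, the bias is zero. If the neediest families attend more, it runs against the intervention (+0.47 in the simulation).

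**Adjustment for T1 MSD.** If motivation relates equally to T1 and T2 MSD and these correlate 0.5 to 0.7, the adjusted bias is roughly the unadjusted one times (1 − correlation): from −0.17 × 0.3 = −0.05 to −0.41 × 0.5 = −0.21. Simulation agrees.

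**Limits of the complier estimate.** It equals the intention-to-treat difference divided by the difference in receipt.
- *Precision.* The intention-to-treat standard error is 3 × √(2/71) = 0.50. At 60% attendance without contamination the complier standard error is about 0.50/0.6 = 0.84, against 0.58 for per-protocol.
- *Exclusion restriction.* Suppose allocation alone shifts self-report by 0.5 items. The complier estimate is then off by 0.5/(0.7 − 0.1) = 0.83 or 0.5/(0.5 − 0.1) = 1.25 items. Simulation gave −0.84 and −1.27, rejecting in about 16% to 17% of trials. Per-protocol was also off, at −0.82 and −0.95.

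**The case against.** Intention-to-treat is primary, per-protocol is openly secondary, and no stated conclusion rests on it. The per-protocol set and its covariates may be defined in a full protocol or analysis plan that is not shown, so their absence from an article is no fault. The size above rests on assumed rates and correlations, and T1 adjustment removes half or more of it. The complier estimate has its own weak spot: families know whether they are waitlisted, and they report the outcome themselves.

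All of that stands, and it limits the point to an improvement of a secondary analysis. It does not remove it. Per-protocol is a stated choice, adjustment leaves unmeasured selection, and the receipt data that usually rule out a complier analysis are planned.

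Three stronger readings are tempting, and the article does not support them:
- **That uptake tracks readiness for change.** The Background says readiness matters for behaviour change; no section links it to counselling attendance or to MSD.
- **That high non-attendance or substantial crossover is expected.** The article speaks of a risk and gives no rate. The 50% uptake in the Sample size section concerns eligible families, not attendance after randomisation.
- **That a complier estimate could not show a false benefit and should replace per-protocol.** Its protection is conditional on the exclusion restriction, and a breach is magnified.

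**Conclusion.** The point holds as a modest one. The planned per-protocol comparison, in its usual form, conditions on behaviour after randomisation and can be biased in either direction. If motivated families attend more and lack fewer items, it shows a spurious benefit of about 0.2 to 0.4 items at 60% attendance with no true effect, or 17% to 41% of the 1-item target, and less after T1 adjustment. Those figures illustrate the mechanism; they do not predict this trial's bias. A complier-average causal effect avoids this selection provided allocation acts only through counselling. It does not repair bias from missing outcomes, which matters because "Loss to follow-up is projected at 50" per cent. The primary analysis is untouched.

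**What to change.** - Add a complier-average causal effect as the secondary analysis of counselling received: two-stage least squares with randomised arm as instrument; at least one counselling meeting before T2, from records in both arms, as exposure; adjustment for T1 MSD and BVC.
- State the exclusion restriction and monotonicity (no family would attend if waitlisted but not if referred at once). Say that unblinded self-report may breach the former, that the method magnifies any such bias, and that it does not correct for loss to follow-up.
- Keep per-protocol, label it exploratory, and define its set.
- Report receipt of counselling by arm beside both results.

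The cost is one extra standard model, a few sentences and a wider confidence interval. No new data are needed.
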